### Study objectives

The primary study objective is to evaluate the safety and efficacy of resections with or without mapping techniques (neurological morbidity and extent of resection) in HGG patients as expressed by National Institute of Health Stroke Scale (NIHSS) scores and volumetric data. Secondary study objectives are to study the overall survival (OS), progression-free survival (PFS) and oncofunctional outcome after resections with or without mapping techniques as expressed by survival data, progression on MRI scans and combining postoperative volumetric/functional outcomes, respectively.

### Study setting and participants

Patients will be recruited for the study from the neurosurgical or neurological outpatient clinic or through referral from general hospitals of the participating neurosurgical hospitals, located in Europe and the USA. The study is open to additional participating neurosurgical centres.

### Patient and public involvement statement

Patients enrolled in the SAFE-trial (awake craniotomy vs craniotomy under general anesthesia for glioblastoma patients, NCT03861299) were consulted for this study to include patient experiences with resections with and without mapping.

### Inclusion criteria

In order to be eligible to participate in this study, a subject must meet all of the following criteria:

Age ≥18 years and ≤90 years.Tumour diagnosed as HGG (WHO grade III/IV) on MRI as assessed by the neurosurgeon.Tumours situated in or near eloquent areas; motor cortex, sensory cortex, subcortical pyramidal tract, speech areas or visual areas as indicated on MRI (Sawaya grading II and II).^19^The tumour is suitable for resection (according to neurosurgeon).Written informed consent.

### Exclusion criteria

A potential subject who meets any of the following criteria will be excluded from participation in this study:

Tumours of the cerebellum, brainstem or midline.Multifocal contrast enhancing lesions.Medical reasons precluding MRI (eg, pacemaker).Inability to give written informed consent.Secondary HGG due to malignant transformation from LGG.Second primary malignancy within the past 5 years with the exception of adequately treated in situ carcinoma of any organ or basal cell carcinoma of the skin.

### Interventions

(1) Awake craniotomy with local anaesthesia (arm 1: awake mapping).

On the evening before surgery 1.5–2.0 mg lorazepam is administered for anxiolysis and 2×8 mg dexamethason. The patient is sedated with a bolus injection of propofol (0.5–1 mg/kg) and kept sedated with a propofol infusion pump (mean: 4 mg/kg/hour) and remifentanil ((0.5–2 µg/kg/min). Supplemental O_2_ might be provided through a nasal cannula. Patients typically receive 1–2 g of cefazolin and sometimes up to 1 g/kg of mannitol (all verified with the surgeon). The room is kept warm and patient covered as the goal is to have the core temperature above 36°C during motor mapping. An arterial line (with standard monitoring for vital signs in addition to BP monitoring), central venous catheter, and urinary catheter are inserted. The patient is awakened and positioned on the table. At this point local anaesthesia for the fixation of the head in the Mayfield clamp and the surgical field is provided with a mixture of 10 mL lidocaine 2% with 10 mL bupivacaine 0.5% plus epinephrine 1:200 000 for the Mayfield clamp and up to 40 mL bupivacaine 0.375% with epinephrine 1:200 000 for the surgical field. After positioning, clamp fixation and surgical field infiltration, patients are sedated again for the trephination until the dura mater is opened, after local application of some drops of local anaesthetics. Propofol sedation is stopped after opening of the dura, with the patient awakening with as few external stimuli as possible. Cortical stimulation is performed with a bipolar electrical stimulator. The distance between both poles is 5 mm, and stimulation is performed by placing this bipolar pincet directly on the cortical surface and stimulating with increasing electrical biphasic currents of 2–12 mA (1–2 mA increasing steps, pulse frequency 60 Hz, single pulse phase duration of 100 µs) until motor or speech arrest is observed. For motor mapping a 2 s train and for speech mapping a 5 s train is used, respectively. The intraoperative neurolinguistic test-battery is performed by a neuropsychologist/linguist, who will inform the neurosurgeon of any kind of speech arrest or dysarthria. The difference between these is not always clear, but can be distinguished from involuntary muscle contraction affecting speech. When localising the motor and sensory cortex, the patient is asked to report any unintended movement or sensation in extremities or face. Confirmed functional cortical areas are marked with a number. After completion of cortical mapping, a resection of the tumour is performed as radical as possible using an ultrasonic aspirator and suction tube, while sparing these functional areas. When the tumour margins or white matter is encountered or when on regular neuronavigation the eloquent white matter tracts are thought to be in close proximity, subcortical stimulation (biphasic currents of 8–16 mA, 1–2 mA increasing steps, pulse frequency 60 Hz, single pulse phase duration of 100 µs, 2 s train) is performed to localise functional tracts. If subcortical tracts are identified, resection is stopped. During the resection of the lesion close to an eloquent area, the patient is involved in a continuous dialogue with the neuropsychologist. That way the neurosurgeon has ‘online’-control of these eloquent areas. In case of beginning disturbances of communication or of motor or sensory sensations the resection is cessated immediately. When, due to stimulation, an epileptic seizure occurs, this is stopped by administering some drops of iced saline on the just stimulated cortical area. If a seizure continues, an intravenous propofol or diphantoin bolus of 0.5 mg/kg is administrated and repeated until the seizure stops. The mapping procedure is temporarily halted. If the patient is adequate, cooperative and able to carry out tasks after the seizure, the mapping procedure can continue. In the case of refractory seizures, the mapping procedure will be permanently halted and the resection will continue under GA. After resection of the tumour a final neurological examination is performed. During closure of the surgical field the patient is sedated with propofol again. After wound closure and dressing, sedation is stopped. The awake patient is transferred to the post-anaesthesia care unit (PACU), where the patient is haemodynamically and neurologically monitored for 24 hours.

(2) Asleep mapping under GA (arm 2: asleep mapping).

UCSF protocol: an intravenous is started on ipsilateral hand to the tumour. The patient is premedicated with up to 2 mg of midazolam. None if altered mental status (prevent further increase in ICP). Arterial (ipsilateral to tumour) catheter is inserted after induction of anaesthesia. Anaesthesia goals are to decrease ICP (if high), to maintain adequate CPP (at least 70 mm Hg) to prevent cerebral ischaemia from brain retraction, and to allow intraoperative cortical motor mapping. Patients typically receive 1–2 g of cefazolin, and 4 mg of decadron before skin incision, and sometimes up to 1 g/kg of mannitol (all verified with the surgeon). The room is kept warm and patient covered as the goal is to have the core temperature above 36°C during motor mapping. Induction with propofol. In case of increased ICP, have patient hyperventilate during preoxygenation and continue hyperventilation with mask as soon as possible after induction of anaesthesia. Fentanyl up to 5 µg/kg in divided doses throughout induction, prior to intubation. Adequate neuromuscular blockade (rocuronium) is verified prior to intubation to avoid coughing/straining. Eyes are taped, and at least one additional large bore intravenous is inserted. Neuromuscular relaxation is let to wear off for motor mapping (do not reverse). The patient position will depend on location of tumour. Anaesthesia is mainained with 70% nitrous oxide in oxygen, low-dose inhalation agent (less than 0.5 MAC), and a remifentanil (0.2 µg/kg/min) or fentanyl infusion (2 µg/kg/hour). Euvolaemia is maintained (Lactated Ringer’s). Mild hyperventilation (PaCO2 35 mm Hg) is used. Once the bone flap is removed, the surgeon assesses the tightness of the dura. ICP is further decreased if necessary (pCO2, mannitol, propofol, head up, etc). Once the dura is open, the goal is to avoid brain shift so that stereotactic navigation system can be used optimally. During motor mapping, the arm, leg and face are uncovered to observe for movement. Stimulation is performed with the use of evoked potentials and continuous dynamic mapping/direct subcortical stimulation (CDM) with a monopolar stimulator (INOMED Medizintechnik, Germany). During stimulation, TES/MEP (transcranial evoked stimulation/motor evoked stimulation) registration is performed of the contralateral m. orbicularis oris, m. orbicularis oculi, m. biceps brachii, m. abductor pollicis, m. rectus femoris and m. tibialis anterior; and the ipsilateral m. abductor pollicis. SSEP (somatosensory evoked stimulation) registration is performed of the contralateral n. tibialis and bilateral n. medianus. The pulse form is negative, with five pulses and a pulse width of 500 µs, ISI 4 and current between 5 and 20 mA. In case of poststimulation continuation of motor activity, the surgeon will try to stop it by applying cold saline on the cortex. Have propofol (10 mg/mL) in line in case of intraoperative seizures (0.5 mg/kg for seizure suppression). May use neuromuscular relaxants after the last motor mapping. Fentanyl infusion is usually stopped at the beginning of closure. Remifentanil infusion is stopped about 10 min before end of surgery. At this point, use of inhalation agent may be replaced with a propofol infusion (50–100 µg/kg/min). pCO2 is normalised to facilitate spontaneous breathing at the end of the operation. Use of inhalation agents (or propofol) is usually stopped about 10–15 min before end of surgery, and nitrous oxide at the end of surgery. Residual neuromuscular blockade is reversed once the Mayfield pins have been removed. At the end of the procedure all anaesthetics are stopped and patient is brought to the PACU (PACU/IC). Detubation of the patient is performed as early as possible, if patient fulfils the detubation criteria (>36°C body temperature, stable haemodynamics, sufficient spontaneous ventilation, adequate response to verbal orders). Postoperative analgesia is provided with paracetamol intravenous or p.o. 1 g up to 4 dd and morphine 7.5 mg SC up to 4 dd, if necessary. At the PACU the patient is haemodynamically and neurologically monitored for 24 hours.

Bern protocol: the following details are different to the above-mentioned protocol. Total intravenous anesthesia without inhalation agents is used (TIVA-only). A bolus of propofol is started (1–2mg/kg body weight) with fentanyl (1–2 mg/kg body weight), and remifentanil (1–2 mg/kg body weight) and maintained with propofol (100–200 mg/kg/min) and remifentanil (0.5 mg/kg/h). A short-acting relaxant is used (Esmeron 0.6 mg/kg body weight for the purpose of intubation. Then, the ‘train-of-four’ technique is used involving percutaneous stimulation of the right median nerve (40 mA, 0.2- msec pulse duration) to test recovery from muscle relaxation. MEPs are recorded from subdermal electrodes in order to quantify the evoked responses. A combination of DCS MEP via a four-contact strip electrode placed on the pre-central gyrus for focal and selective stimulation and a back-up TES MEP via scalp electrodes is used.^20^ The ‘suction probe’ (INOMED medizintechnik, Germany; #525 650) is used for cortical mapping and subcortical continuous dynamic mapping.^21^ For subcortical stimulation a monopolar cathodal pulse stimulation is used with train of 5 pulses of 0.5 msec duration, ISI 4 msec and 2 Hz repetition rate. The mapping intensities range from 20 mA down to 3 mA (and in selective cases down to 1mA). Monitoring motor function is continued until dura closure in order to detect vascular injuries (for instance due to vasospasms).

(3) Craniotomy under GA without mapping (arm 3: no mapping).

On the evening before surgery, 1.5–2.0 mg lorazepam is administered for anxiolysis.Sixtey min before anaesthesia induction, the patient receives 1 g paracetamol orally and 7.5–15 mg midazolam orally if requested for sedation. En route to the operating room, 0.5–2 mg midazolam intravenous may be given. 1 g cefazoline is given intravenous for antibiotic prophylaxis before anaesthesia induction. GA is induced intravenously with fentanyl 0.25–0.5 mg, propofol 100–200 mg and cis-atracurium 10–20 mg. After induction of anaesthesia, the patient is orotracheally intubated and mechanical ventilation is applied. Respiratory rate and tidal volume are adjusted to keep the patient normocapnic.

An arterial line (alternatively: two peripheral intravenous), central venous catheter (v. basilica) and urinary catheter are inserted. Anaesthesia is maintained with propofol (up to 10 mg/kg/hour) and remifentanil (0.5–2 µg/kg/min). isoflurane (up to 1 MAC) and clonidine (1–2 µg/kg) may be added for maintenance, if necessary (a beta blocker or calcium channel blocker may be used to control BP as an alternative to clonidine). The fluid management is aiming for normovolaemia. 0.9% saline solution and balanced crystalloids are used for maintenance, in case of blood loss >300 mL, HAES 130/0.4 solution (hydroxyethyl starch) will be given. Temperature management is aiming for normothermia, warm-air blankets and warmed infusion lines are used. Arterial blood gas analysis is performed at the beginning of the procedure and repeated, if necessary. Electrolytes are controlled and substituted and hyperglycaemic will be treated with insulin, if necessary. The anaesthetised patient is positioned on the table. Local infiltration of the scalp is performed with 20 mL lidocaine 1% with epinephrine 1:200.000 to reduce bleeding. The insertion points of the Mayfield clamp are not infiltrated with local anaesthetics.

Trephination and tumour resection are performed without any additional neuro-psychological monitoring, guided by standard neuronavigation. At the end of the procedure, all anaesthetics are stopped and patient is brought to the PACU. Detubation of the patient is performed as early as possible, if patient fulfils the detubation criteria (>36°C body temperature, stable haemodynamics, sufficient spontaneous ventilation, adequate response to verbal orders). Postoperative analgesia is provided with paracetamol intravenously or orally 1 g up to 4 dd and morphine 7.5 mg SC up to 4 dd, if necessary. At the PACU the patient is haemodynamically and neurologically monitored for 24 hours.

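### Bern asleep-mapping regimen: propofol maintenance and the fentanyl bolus are wrong as printed (mg where µg is evidently meant), and both remifentanil doses need checking at source

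*Protocol article*

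**What the plan says.** The Interventions section describes two versions of arm 2 (asleep mapping). The UCSF version comes first. The Bern version follows as a list of differences from it and uses intravenous anaesthesia only.

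- **Bern, induction:** "A bolus of propofol is started (1–2mg/kg body weight) with fentanyl (1–2 mg/kg body weight), and remifentanil (1–2 mg/kg body weight").
- **Bern, maintenance:** "maintained with propofol (100–200 mg/kg/min) and remifentanil (0.5 mg/kg/h").

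The same section gives doses of the same drugs elsewhere:

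- **Arm 2, UCSF:** fentanyl at induction, "Fentanyl up to 5 µg/kg in divided doses throughout induction, prior to intubation"; maintenance opioid, "a remifentanil (0.2 µg/kg/min) or fentanyl infusion (2 µg/kg/hour"); near the end of surgery, "use of inhalation agent may be replaced with a propofol infusion (50–100 µg/kg/min").
- **Arm 1, awake mapping:** "kept sedated with a propofol infusion pump (mean: 4 mg/kg/hour) and remifentanil ((0.5–2 µg/kg/min").
- **Arm 3, no mapping:** induction, "GA is induced intravenously with fentanyl 0.25–0.5 mg, propofol 100–200 mg and cis-atracurium 10–20 mg"; maintenance, "Anaesthesia is maintained with propofol (up to 10 mg/kg/hour) and remifentanil (0.5–2 µg/kg/min").

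Nothing in the article explains or corrects the Bern units.

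**The concern.** The Bern paragraph states every dose in mg. For propofol maintenance and the fentanyl bolus, that puts the figures hundreds of times or more above what the article gives for the same drugs elsewhere. A difference in practice between centres cannot explain a gap of that size. The remifentanil doses also look too high, but the likely correction is less clear.

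These are stated doses in the section that defines a study arm, and further centres may still join (Study setting and participants; Trial status). Followed as written, they would be dangerous or impossible to give. The risk is limited, because the paragraph describes one centre's regimen and no other centre is told to adopt it.

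**Working it through.** The doses are prescribed rather than derived, so the article has no calculation of its own to reproduce. The check is unit conversion and comparison with the article's other doses. Ratios of per-kg doses do not depend on body weight. Where a weight is needed, 70 kg (range 50–100 kg) is assumed; the article gives none.

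**1. Propofol maintenance (Bern: 100–200 mg/kg/min)**

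- Per hour: 100 × 60 = 6,000 and 200 × 60 = 12,000 mg/kg/h.
- Against the arm 3 maximum of 10 mg/kg/h: 6,000/10 = 600 and 12,000/10 = 1,200 times.
- Against the UCSF infusion, matching range ends: 100,000/50 = 200,000/100 = 2,000 times. Crossing the range ends gives 100,000/100 = 1,000 to 200,000/50 = 4,000 times.
- Against the Bern bolus of 1–2 mg/kg, matching range ends: 100/1 = 200/2 = 100 boluses every minute.
- Volume at 70 kg and the 10 mg/mL solution named in the UCSF text: 100 × 70/10 = 700 to 200 × 70/10 = 1,400 mL per minute, which cannot be given.
- Read as µg: 100–200 × 60/1,000 = 6–12 mg/kg/h, at most 1.2 times the arm 3 maximum.

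**2. Fentanyl bolus (Bern: 1–2 mg/kg)**

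- Against the UCSF ceiling of 5 µg/kg: 1,000/5 = 200 and 2,000/5 = 400 times.
- Against arm 3 (0.25–0.5 mg in total) at 70 kg: 70–140 mg; 70/0.25 = 140/0.5 = 280 times. Over 50–100 kg and all range ends: 50/0.5 = 100 to 200/0.25 = 800 times.
- Read as µg: 1–2 µg/kg, within the UCSF ceiling. At 70 kg this is 0.07–0.14 mg, below the arm 3 dose but no longer hundreds of times away from it.

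**3. Remifentanil maintenance (Bern: 0.5 mg/kg/h)**

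| Reading | Rate, µg/kg/min | Against UCSF (0.2) | Against arms 1 and 3 (0.5–2) |
|---|---|---|---|
| As printed | 500/60 = 8.33 | 8.33/0.2 = 42 times above | 8.33/2 = 4.2 to 8.33/0.5 = 16.7 times above |
| µg for mg only | 0.5/60 = 0.0083 | 0.2/0.0083 = 24 times below | 0.5/0.0083 = 60 to 2/0.0083 = 240 times below |
| µg for mg and min for h | 0.5 | 0.5/0.2 = 2.5 times above | at the lower end of the range |

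Changing the mass unit alone does not bring this dose into line, so the mass unit, the time unit or the number may be wrong.

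**4. Remifentanil bolus (Bern: 1–2 mg/kg)**

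The article gives no other remifentanil bolus. At its highest infusion rate, 2 µg/kg/min, the bolus equals 1,000/2 = 500 to 2,000/2 = 1,000 minutes of infusion. That makes the mg unit implausible but does not prove an error.

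**5. Propofol bolus (Bern: 1–2 mg/kg)**

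The arm 3 dose of 100–200 mg at 50–100 kg is 100/100 = 1 to 200/50 = 4 mg/kg, which covers 1–2 mg/kg. This dose is not questioned.

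**The case against.** The strongest objection is that the µ sign may have been lost in typesetting or when the text was read. The Bern paragraph contains no µ at all, and its different style suggests text supplied separately. This cannot be ruled out. It is unlikely, because µ appears correctly in the arm 1, UCSF and arm 3 texts. Restoring it would also leave remifentanil maintenance 24–240 times too low, so a source check is needed in any case. What stands is that the doses are shown to be wrong in the article as we have it; whether the full protocol is wrong is unknown.

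Some comparators are also imperfect. The UCSF propofol infusion replaces the inhalation agent near the end of surgery, UCSF remifentanil is given with nitrous oxide and an inhalation agent, and arm 1 is sedation for awake surgery. That is fair, and those ratios show only orders of magnitude. The propofol error does not depend on them: arm 3 is general anaesthesia with propofol maintenance and is enough by itself. The fentanyl comparison is induction against induction.

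The two remifentanil doses are queries, not demonstrated errors. That is accepted, and they are put as queries here.

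Finally, the study is observational and its treatments are care-as-usual (Study monitoring). An anaesthetist would be expected to notice the propofol and fentanyl doses. This limits the severity, but it does not make the printed doses right.

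**Conclusion.** The point holds, as a minor safety matter. Two doses are wrong as printed, with high confidence: propofol maintenance, at 600–1,200 times the arm 3 maximum, and the fentanyl bolus, at 200–400 times the UCSF ceiling. Neither ratio depends on an assumed body weight.

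Both remifentanil doses need checking. Maintenance is 4–17 times the arm 1 and arm 3 rates as printed, a smaller discrepancy than the other two and so perhaps the easiest to overlook (a judgement, not something the article shows). The intended value of neither remifentanil dose can be recovered from the article.

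Design, sample size and analysis are unaffected.

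**What to change.** Check four items in the Bern paragraph against the full protocol or the centre's own regimen:

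1. The mass unit of the propofol infusion; evidently 100–200 µg/kg/min.
2. The mass unit of the fentanyl bolus; evidently 1–2 µg/kg.
3. The mass unit of the remifentanil bolus.
4. The mass unit, time unit and number of the remifentanil infusion.

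Then correct the article: items 1 and 2 to µg once the source confirms them, and items 3 and 4 to whatever the source gives. Do not replace every mg by µg, since that would spoil the propofol bolus and leave remifentanil maintenance far too low. Notify sites only if the text they hold has the same error; only the article is available here.

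The cost is a source check and a text correction, plus a short note to sites if needed.

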### Surgical adjuncts and additional imaging

The use of fMRI, Diffusion Tensor Imaging (DTI), ultrasound or 5-ALA (5-aminolevulinic acid) is allowed to be used in all groups on the surgeon’s indication.

### Participant timeline

The flow diagram illustrates the main study procedures, including follow-up evaluations (figure 1). In summary, study patients are allocated to either the awake mapping, asleep mapping or no mapping group and will undergo evaluation at presentation (baseline) and during the follow-up period at 6 weeks, 3 months, 6 months and 12 months postoperatively. Motor function will be evaluated using the NIHSS and Medical Research Council (MRC) scales. Language function will be evaluated using a standard neurolinguistic test-battery consisting of the Aphasia Bedside Check (ABC), Shortened Token Test, Verbal fluency, Picture description and Object naming. Cognitive function will be assessed using the Montreal Cognitive Assessment (MoCA). Patient functioning with be assessed with the Karnofsky Performance Scale (KPS) and the ASA (American Society of Anesthesiologists) physical status classification system. Health-related quality of life (HRQoL) will be assessed with the EQ-5D questionnaire (EuroQol Five Dimensions health questionnaire) and the QLQ-C30 and QLQ-BN20 questionnaires. OS and PFS will be assessed at 12 months postoperatively. We expect to complete patient inclusion in 4 years. The estimated duration of the study (including follow-up) will be 5 years.

